# SYNOPSIS

| SPONSOR | **Centre Oscar LAMBRET**  [name]  [name]  [name]  **[contact] - **[contact] |
| --- | --- |
| INDICATION | Intermediate risk prostate cancer |
| **TITLE** | ***Intermediate risk prostate cancer : Prospective phase II study evaluating hypofractionated stereotactic boost irradiation*** |
| **PRINCIPAL INVESTIGATOR**  **(CyberKnife treatment)**  **Co-PRINCIPAL INVESTIGATOR**  **(LINAC treatment)** | **[name] [name]**  Radiation Oncology University Department  [contact] – [contact]  email: [[contact]](mailto:[contact])  **[name] [name]**  Radiation Oncology Department  Centre Hospitalier Lyon Sud  [name]  [contact] – [contact]  email: [[contact]](mailto:[contact]) |
| **METHODOLOGY** | Phase II multicentric biomedical research evaluating the feasibility of hypofractionated stereotactic boost irradiation in patients presenting with intermediate risk prostate cancer |
| **NUMBER OF CENTERS** | 8 |
| **OBJECTIVES** | **Primary**   - Evaluate urinary and rectal toxicity according to the NCI-CTCAE v3.0 scale of conventional radiotherapy to 46Gy (prostate and seminal vesicles) followed by a 3 x 6 Gy stereotactic boost (prostate only) administered either with CyberKnife or with a linear accelerator.   **Secondary**   - Evaluate local control at 3 years - Determine the overall survival without metastatic disease - Evaluate survival without biological failure at 3 years - Evaluate technical criteria: implantation of fiducial markers, treatment time, cumulative dosimetry, administration and length of boost session - Study PSA kinetics during treatment course (between the two irradiation phases) and after treatment - Evaluate sexual dysfunction caused by this therapeutic strategy - Evaluate urinary discomfort |
| **INCLUSION CRITERIA** | - Prostate Adenocarcinoma, histologically proven - With at least one of the following criteria : - T2b - and/or PSA between 10 and 20 ng/ml - and/or Gleason Score equal to 7 - Prostate volume ≤ 80 cc - Absence of lymph node involvement (adenopathy < 1.5 cm on scanner or MRI, and/or negative lymph node dissection) - Absence of metastasis (bone scintigraphy) - Age  18 years - Absence of previous pelvic irradiation - Absence of previous antitumoral treatment, including prostatectomy and/or hormonotherapy - Good general condition: ECOG  1 (appendix 3) - Absence of contraindication to the placement of fiducial markers – hemostasis problems shall be corrected before implantation - Life expectancy greater or equal to 10 weeks - Patient affiliated with a health insurance system - Patient having signed the informed consent |
| EXCLUSION CRITERIA | - Absence of histological proof - Unfavorable stage (T2c and/or PSA > 20 ng/ml and/or Gleason > 7) - Favorable stage (T1c T2a and PSA < 10 ng/ml and Gleason < 7) - Prior history of uncontrolled cancer and/or treated for less than 5 years (except basocellular skin cancer) - Contraindication to MRI - IPSS score >10 - Recurrent or metastatic disease - Known gold allergy - Patient already included in another therapeutic trial of an experimental drug - Unavailability to medical follow-up for geographical, social or psychological reasons |
| **NUMBER OF PATIENTS** | 76 patients receiving hypofractionated stereotactic boost irradiation :  - 38 by CyberKnife  - 38 by linear accelerator |
| **STUDY DURATION** | Start of the study: September 2009  End of enrollment: September 2012  End of study: December 2015 |
| **ASSESSMENT CRITERIA** | Primary  Urinary or rectal toxicity: According to the NCI-CTCAE v3.0 rating scale (appendix 10). Acute toxicities are defined as all toxicities occurring in the 6 months following the start of radiotherapy. Late toxicities are defined as all toxicities occurring beyond 6 months.  **Secondary**   - Rate of local control at 3 years: non progression of : - PSA level according to the Phoenix definition (nadir to be obtained) - Clinical examination (rectal touch) - No pathological signal on MRI - Median time without progression for the entire cohort: interval between the date of inclusion and the date of progression, whether clinical (rectal touch) or radiological (prostatic MRI). - Median overall survival: Median time for the entire cohort comprising the time between the date of inclusion and the date of death, whatever the cause. - Survival without biological failure at 3 years: Phoenix criteria for PSA increase (nadir + 2 ng/ml) (see chapter 6.7.3) - Technical criteria: Implantation of markers, treatment time, cumulative dosimetry, administration and length of boost session - PSA kinetics during the entire treatment (between the two irradiation phases) and after treatment - Sexual dysfunction = international questionnaire IIEF 5 - Urinary discomfort = IPSS questionnaire |
| **STATISTICAL ANALYSIS** | The initial characteristics of included patients will be presented in the form of summary tables. Continuous variables will be summarized by conventional descriptive statistics parameters (median and outlying  values, mean and standard deviation when necessary). Category variables will be presented in the form of contingency tables (absolute frequency and percentage of each modality), additionally stating the number of missing data, along with the 95% confidence interval.  Subject inclusion and exclusion criteria will be checked against data entered into the case report forms when possible. Any deviations from the protocol will be documented.  Survival will be analyzed by the Kaplan-Meier nonparametric method. |
| **BRIEF DESCRIPTION OF PRODUCTS AND COURSE OF TREATMENT** | - Information provided, collection of consent - Recommended implantation of intra-prostatic markers (fiducials) (see appendix 7 and concomitant treatment 7.6) - Treatment planning - 3D radiotherapy with or without IMRT over 31 to 42 days, 23 x 2Gy/fraction, for a total total of 46 Gy - Stereotactic boost irradiation, 3 x 6 Gy over 5 to 9 days : - delivered by CyberKnife for patients treated in the following centers: Centre Oscar Lambret – Lille, Centre Antoine Lacassagne – Nice, Centre Alexis Vautrin – Nancy - delivered by linear accelerator for patients treated in the other centers |

# 4 INTRODUCTION AND STUDY RATIONALE

## 4.1 Incidence

In France, prostate cancer has become the most frequent cancer in men after age 50 and represents almost 25% of all new cancers in men. The number of cases discovered annually is becoming, in certain regions, superior to the incidence of breast cancer, with an estimated incidence in 2005 of 62,000 according to data from the general cancer registries (Francim). Between 1975 and 2000, an annual increase of 4.8% in the incidence has been noted. The aging of the population cannot completely explain this net increase, which is concomitant with the widespread use of PSA testing and the diffusion of systematic echo-guided techniques of prostate biopsy (120 to 150,000 prostate biopsies performed in France annually). The median age at diagnosis is decreasing (currently around 70 years); it was 74 years in 1995. The probability that a French male will be discovered to have prostate cancer during the course of his life was estimated at 7.9% in 1992 and at 13% in 1998 (i.e., 1 man in 8 less than 75 years old).

## 4.2 Mortality

Prostate cancer is the second leading cause of death by cancer in men after lung cancer and the 4th overall cause of death by cancer. With 10,004 deaths in 2000, it represents 10% of cancer deaths in men (crude death rate: 35.1/106 men). The mortality rate from prostate cancer has increased by 0.17% per year from 1980 to 2000, but the study undertaken between 1990 and 1996 demonstrated that the mortality rate had decreased by 3.3% per year in five French departments, with a stable mortality adjusted by age since 1980. The risk of developing prostate cancer is increasing for younger age groups. For a man born in 1928, the risk of developing prostate cancer before 75 years (cumulative rate) is estimated at 7.3%. This risk is multiplied by 2.97 for a man born in 1943 and almost by 5 for a man born in 1953, if the current trend continues.

In 1995, the French incidence rate was slightly above the mean of European Union countries (after Finland, Sweden, Holland, Belgium, Ireland, Germany and Austria). The mortality rate remains relatively homogenous among these countries. Mortality seems to decrease in some countries (Canada, United Kingdom, Italy, United States, Austria), without being explained solely by screening (not done in the UK). Only the results (expected in 2 to 4 years) of randomized screening studies will allow a conclusion on the effect of screening in regards to mortality.

## 4.3 Study Justification

### 4.3.1 Radiotherapy for localized prostate cancer

Radiotherapy has demonstrated curative efficacy in prostate cancer at the localized stage [Bey 2002, Soulié 2004]. Conformal radiotherapy [Dubray 1999] relies on CT imaging in order to precisely identify the anatomic location of target volumes (prostate, seminal vesicles) and healthy organs (rectum, bladder, femoral heads). Computerized tools for the reconstruction of images - “views of the treatment beam” - allow individualized adaptation of the shape of the beam in order to optimize irradiation ballistics. The contribution of different beams is then confirmed during preliminary dosimetric planning, using computer programs to calculate the distribution of expected doses in a three dimensional representation of the patient.

Two randomized studies have demonstrated that conformal irradiation decreased early and late digestive toxicity [Dearneley 1999, Koper 2004]. This benefit is the result of a better delineation of the prostate and conformality of the beam and consequently a reduction of the volume of irradiated healthy tissue. The total recommended doses are from 70 Gy in 35 sessions of 2 Gy for low risk cancers, and at least 74 Gy (37 sessions of 2 Gy) for intermediate or higher risk cancers [Soulié 2004].

### 4.3.2 Hypofractionated Radiation Therapy

An abundant clinical and experimental literature has demonstrated that the administration of doses superior to 2 Gy per session significantly increases the risk of late irradiation sequelae [partial review in Brenner 2004]. Therefore, the dose is usually of 2 Gy per fraction and the consequence is a radiation therapy treatment lasting 2 months (35 to 40 fractions, 5 fractions per week). Considering the total dose to administer, patients with prostate cancer are having radiotherapy proposed to them over almost 2 months (35 to 40 sessions at a rate of 5 sessions per week).

Doses superior to 2 Gy per session (hypofractionated radiotherapy) are traditionally used for palliative treatments, or for patients whose life expectancy is short. However, since the end of the 1990s, several publications have raised interest in delivering higher dose per fraction, (hypofractionated radiotherapy) for prostate cancer.

Analysis of patient populations treated with external beam therapy or brachytherapy with the help of a mathematical model integrating the impact of fractionation has suggested that doses per session greater than 2 Gy would increase antitumoral efficacy [Brenner 2002, Fowler 2003, Bentzen 2005]. Following the example of healthy tissues, repair of radio-induced lesions would be less effective in prostate cancers than in the majority of tumors, hence a greater biological efficacy of hypofractionated irradiation.

Based on these recent data, some teams [Junius 2007, Livsey 2003, Yeoh 2003] have published promising results in terms of efficacy and tolerance.

The development of radiotherapy under conformal conditions allows better protection of healthy tissues, and so probably the reduction of the harmful effects of hypofractionated radiotherapy.

### 4.3.3 Importance of the irradiation total dose

Five randomized prostatic studies report an improvement in the rate of biological control at 5 years with an increase dose of irradiation without a major increase in the complication rate (Albertsen 1996, Bey 2002, Amer 2003, Beckendorf 2004, Bentzen 2005). These studies are as much on conformal radiotherapy with or without intensity modu-lation as on high or low dose rate brachytherapy (Bey 2002). The brachytherapy boost techniques are close to ablative treatments, as demonstrated by a very rapid drop in PSA levels and the rapid normalization of spectroscopic examinations compared to external beam radiotherapy alone (Brenner 2004).

With a long enough follow-up, the relation between biochemical control, decrease of distant spread, and perhaps survival appears clearer and clearer (Brenner 2002, Chirpaz, 2002, Dearnaley 1999, Dubray 1994-1999). However, it is possible that the high doses currently administered are still not high enough to obtain the highest rates of biochemical control considering the presence of residual hypoxic zones in the prostate (Fayers 1995). Additional benefit could be obtained with higher doses with a biological equivalence (EQD2 of 100 Gy for a α/β of 3Gy (AFU 2002 guidelines). Consequently it is probable that we have not yet reached the optimal dose levels with current techniques of prostate radiotherapy, although numerous technological improvements are still possible.

### 4.3.4 Stereotactic radiation therapy concept

The concept of stereotactic radiotherapy consists of delivering a high irradiation dose highly conformal to a small tumor. The result is an “ablation” of the tumor, while preserving the surrounding tissues. This technique requires high precision in the localization of the tumor, and for this reason, was first developed for the treatment of cerebral metastases. Indeed, in immobilizing the skull (and therefore the brain), it is possible to localize an intra-cerebral lesion with precision. Local control results have allowed stereotactic radiotherapy to be proposed as an alternative to surgery in the treatment of cerebral metastases. More recently, the utilization of new technologies in the spatial localization of tumors, such as Cone Beam CT, has allowed the development of this irradiation technique in extra-cranial tumors. The Cone Beam CT allows the acquisition of scanography slices directly on the accelerator table while the patient is already in the treatment position. It has become possible to precisely visualize tumor’s position, even in soft tissues (lung, liver, prostate…). Thus, stereotactic radiotherapy has been used in the irradiation of small size lesions of bronchial cancers (T1 and T2N0). For these tumors, although considered radio-resistant, the local control rate has raised from 30%-40%, after conventional radiotherapy, to 80%-90% after stereotactic radiotherapy (Timmerman 2003 & 2006, Fritz 2006, Nyman 2006, Xia 2006, Hara 2006).

Stereotactic radiation therapy has been developed in other tumoral localizations such as liver (Tse 2008), kidney (Swedman 2008) or prostate.

### 4.3.5 Stereotactic radiotherapy of prostate cancer

Some work has been done on stereotactic radiotherapy for prostate cancer. However, few studies have evaluated this technique either as monotherapy or as a boost to conventional fractionated radiotherapy. Madsen and al reported 40 patients treated with monotherapy stereotactic radiation treatment with a dose of 33.5Gy in 5 fractions [Madsen 2007]. Irradiation was administered with a linear accelerator. The equivalent biological dose was estimated at 78Gy. No late urinary or rectal toxicity was observed and only one acute grade 3 intestinal toxicity was observed. Authors had previously evaluated prostate intra-fraction motion [Madsen 2003]. Following a low-gas, low-motility diet, mean movements were of 2 mm, 1.9 mm and 1.4 mm in the superior-inferior, anterior-posterior and right-left directions respectively. In a similar study, King and al have evaluated the feasibility of CyberKnife stereotactic radiation treatment as monotherapy for localized prostate cancer at a total dose of 36.7Gy in 5 fractions of 7.25Gy each. Only 2 late urinary toxicities of grade 3 were reported. Authors emphasized the necessity of a minimum of 1 day between each fraction in order to prevent severe rectal toxicities. Mantz and al followed the same irradiation protocol in 18 patients with an adenocarcinoma at a favorable stage. The prostatic volume was limited to 60 cc. Irradiation was administered with a Trilogy system (Varian). After few weeks/months of follow-up, only grade 1 rectal toxicities were reported.

Finally, a stereotactic irradiation of prostate (5 x 9 Gy) is on going at Dallas University. Intra-prostatic markers and an endo-rectal balloon are used [Edwards 2007]. Intra-fraction mean prostatic movements are of 2 mm in all directions [Boike 2007].

A second approach is to propose a stereotactic radiotherapy as a boost to conventional irradiation for intermediate risk prostate cancer. Boosts are already delivered by HDR brachytherapy for low or intermediate risk prostate cancer. Usually, 36 to 50Gy are administered on the prostate and the seminal vesicles followed by 3 to 4 brachytherapy sessions of 5 to 6Gy [Hoskin 2007-2008, Demanes 2005, Galalae 2004, Eulau 2000]. Doses delivered at the level of the prostate are higher than the dose delivered with external beam radiation therapy alone. Results are very promising particularly biological control with no significant increase of rectal and urinary complications. However, HDR brachytherapy remains an invasive procedure requiring anesthesia. Stereotactic radiotherapy could potentially deliver doses equivalent to HDR brachytherapy in a non-invasive manner and without anesthesia. Ares and al studied the incidence of late rectal toxicities of a boost delivered either by HDR brachytherapy or stereotactic irradiation [Ares 2007]. Following 3D external beam irradiation to 64-66Gy, a brachy-therapy boost (2 x 5 to 8Gy) was adminisred to 51 patients (Geneva University) and a stereotactic radiotherapy boost was delivered to 43 patients (Barcelona University). No grade 3 rectal toxicity was observed. Grade 1-2 rectal toxicity was slightly higher with stereotactic radiotherapy than with HDR brachytherapy. However, compared to 3D radiotherapy to 74-78Gy, the rate of grade 1-2 rectal toxicity are clearly lower.

The objective of this project is to evaluate the tolerance of high doses by fraction, administered in a stereotactic mode as a boost to external beam therapy in patients with intermediate risk prostate adenocarcinoma [Kattan 2000]. Given the exclusion of unfavorable-risk tumors, hormonotherapy will not be introduced, based on the lack of benefit after high radiation doses for this category of patients [Kattan 2000, Eade 2007]. The goal of this study is also to confirm the data of the William Beaumont Hospital, showing that with an EQD2 of 100 Gy (for an α/β of 3 Gy), a very high level of disease control can be obtained, with a possible impact on overall survival. This approach will also study the kinetics of PSA decrease, indirect indicator of the ablative effects of the irradiation methods, in order to compare them to brachytherapy [Koper 2004].

Stereotactic treatments can be administered with modern radiation therapy equipments. The CyberKnife system, which uses robotics, can deliver treatment with inframillimetric precision and real time tracking of the target. Linear accelerators can entirely deliver precise treatments with the possibility of intensity modulation

These technological advances allow reduction of the dose to healthy tissues surrounding the treatment area and limit the margins traditionally required in order to take movement into account. It therefore becomes possible to deliver a very high dose without major risk of toxicity [Hannoun-Levi 2008].

***Therefore, we propose a phase II multicentric study evaluating the feasibility of external beam radiotherapy at 46Gy combined with boost irradiation by stereotactic radiotherapy (CyberKnife or linear accelerator) in patients presenting with intermediate risk adenocarcinoma of the prostate, with the object of delivering an equivalent biological dose on the order of 80Gy while best preserving critical organs.***

# 5 STUDY OBJECTIVES

## 5.1 Primary objective

- Evaluate urinary and rectal toxicity according to the NCI-CTCAE v3.0 scale of conventional radiotherapy to 46Gy (prostate and seminal vesicles) followed by a 3 x 6Gy stereotactic boost (prostate only) administered either with CyberKnife or with a linear accelerator

## 5.2 Secondary objectives

- Evaluate local control at 3 years
- Determine the overall survival without metastatic disease
- Evaluate survival without biological failure at 3 years
- Evaluate technical criteria: implantation of fiducial markers, cumulative dosimetry, administration and length of boost session
- Study PSA kinetics during treatment (between the two irradiation phases) and after treatment
- Evaluate sexual dysfunction caused by this therapeutic strategy
- Evaluate urinary discomfort

# 6 STUDY DESIGN

## 6.1 Methodology

Phase II multicentric biomedical research evaluating the advantages of hypofractionated stereotactic boost irradiation, done by CyberKnife or linear accelerator, in patients with intermediate risk prostate cancer

## 6.2 Inclusion Criteria

*All the following criteria are necessary for inclusion :*

- Prostate adenocarcinoma, histologically proven
- With at least one of the following intermediate criteria :
- T2b
- and/or PSA between 10 and 20 ng/ml
- and/or Gleason Score equal to 7
- Prostate volume ≤ 80 cc
- Absence of lymph node involvement (adenopathy < 1.5 cm on scanner or MRI, and/or negative lymph node dissection)
- Absence of metastasis (bone scintigraphy)
- Age  18 years
- Absence of previous pelvic irradiation
- Absence of previous antitumoral treatment, including prostatectomy and/or hormonotherapy
- Good general condition: ECOG  1 (appendix 3)
- No contraindication to fiducial markers placement– hemostasis problems shall be corrected before implantation
- Life expectancy greater or equal to 10 weeks
- Patient affiliated with a health insurance system
- Patient having signed the informed consent

## 6.3 Exclusion criteria

*One of the following criteria is sufficient for exclusion:*

- Absence of histological proof
- Unfavorable stage (T2c and/or PSA > 20 ng/ml and/or Gleason > 7)
- Favorable stage (T1c T2a and PSA < 10 ng/ml and Gleason < 7)
- Prior history of uncontrolled cancer and/or treated less than 5 years (except basocellular skin cancer)
- Prostate cancer previously treated with hormonotherapy
- Contraindication to MRI
- IPSS score > 10
- Recurrent or metastatic disease
- Known gold allergy
- Patient already included in another therapeutic trial of an experimental drug
- Unavailability to medical follow-up for geographical, social or psychological reasons

## 6.4 Early study withdrawal criteria

The length of patient participation in the study is at least 3 months after the last radiotherapy session.

The conditions for early termination of the study are :

- Failure to track the tumor
- Failure to place fiducial markers
- Dose-volume histograms (DVH) constraints not achievable
- Interval greater than 3 weeks between the end of the radiation therapy phase and the first session of hypofractionated stereotactic boost irradiation

## 6.5 Termination study criteria

Termination from the study must take place if:

- disease progression

- patient’s decision

- investigator’s decision

- death of the patient

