6.7.2 Evaluation of tumor efficacy

To be deemed assessable, patients must have received **at least 1 session of boost stereotactic irradiation**.

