#### *Global survival*

Time between :

- inclusion date,
- date of death, whatever the cause,
- Patients alive at the time of the analysis will be censored at the date of the last follow-up visit.

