### 6.8.3 Determination of the number of subjects

The number of patients required for this study was calculated using the single step Fleming method with the following hypotheses :

P0 = 85% (level of patients without any toxicity below which the method would provide no

advantage)

P1 = 95% (level of patients without toxicity expected from the proposed methods)

= 5%

= 10% , i.e. a power of 90%

To meet these conditions, the Fleming formula requires 76 evaluable patients to be included (38 by CyberKnife and 38 by linear accelerator). The study's goal will be considered achieved if, of the 76 evaluable patients, at least 70 present no grade 3-4 toxicity according to the NCI scale.

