## 7.5 Subsequent antitumor treatments

In case of tumor progression, the patient will benefit from all treatments relevant to his situation. The patient presenting with distant progression remains in the study. Follow-up will be observed.

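### Section 6.5 ends study participation at disease progression while Section 7.5 and Appendix 2 imply that follow-up continues; if 6.5 is followed, censoring depends on prognosis

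*Protocol*

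**What the plan says.** Section 6.5 opens with "Termination from the study must take place if" and gives four reasons: disease progression, the patient's decision, the investigator's decision, and death. Progression is not restricted to local, biochemical or distant.

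Section 7.5 states: "The patient presenting with distant progression remains in the study. Follow-up will be observed". In Appendix 2, footnote 5 is attached to the MRI row at every post-treatment column, including 48 and 60 months, and excuses MRI where the tumour has already progressed. It does not excuse the visit, the PSA, the questionnaires or the adverse event assessment.

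For overall survival, Section 6.7.2 says: "Patients alive at the time of the analysis will be censored at the date of the last follow-up visit". Metastasis-free survival runs from inclusion to the first metastasis.

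Section 6.4 lists conditions for early termination: failed tracking, failed marker placement, unachievable dose-volume constraints, and "Interval greater than 3 weeks between the end of the radiation therapy phase and the first session of hypofractionated stereotactic boost irradiation". Section 6.7.2, on tumour efficacy, adds "To be deemed assessable, patients must have received" at least one boost session. The Synopsis gives the sample as "76 patients receiving hypofractionated stereotactic boost irradiation". Section 6.8.3 applies the success rule, at least 70 of 76 without grade 3–4 toxicity, to evaluable patients.

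**The concern.** Distant progression is a form of disease progression, so Section 6.5 sends out of the study a patient whom Section 7.5 keeps in. Centres may resolve this differently. What a centre does not collect because it followed 6.5 cannot be recovered by any later analysis plan.

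Two secondary objectives are exposed. Overall and metastasis-free survival depend on following men after a first local progression, and those men are at higher risk of both events. Late toxicity, which is part of the primary criterion, would also lose its scheduled grading from the day of exit.

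Section 6.4 raises a related question. The primary objective in Section 5.1 covers the whole sequence of 46 Gy followed by the boost. A patient who starts radiotherapy but leaves before the boost has still been exposed to part of it.

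**Working it through.** **1. The passages side by side.**

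- Section 6.5: progression of any kind leads to mandatory exit, with a final evaluation under Section 6.6.5.
- Section 7.5: distant progression leads to continued participation and follow-up.
- Appendix 2, footnote 5: after progression MRI is waived, and the rest of the visit stands.

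The first conflicts with the second for distant progression, and with the third for any progression. No passage says which prevails.

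**2. What is lost if Section 6.5 is applied.**

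- Overall survival: the patient is censored at his exit visit and a later death is outside planned follow-up.
- Metastasis-free survival: a metastasis that is itself the first progression is recorded, but one that follows a local progression is not.
- Local control and biochemical failure: little is lost where the failure is itself the event that causes exit.
- Late toxicity: one exit assessment is made, and related serious events remain declarable (Section 6.7.1). Grade 3 need not mean serious. In Appendix 10, urinary frequency of at least once an hour is grade 3.

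Kaplan-Meier estimation treats a censored patient as having the same later risk as those still observed. A man censored because he progressed has a higher risk, so the curve tends to lie too high.

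**3. Size for survival, under assumption.** The protocol states no progression rate. Take 10–15% by 36 months:

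- 0.10 × 76 = 7.6, or 8 men; 0.15 × 76 = 11.4, or 11 men.
- The Kaplan-Meier estimate cannot exceed the value obtained by counting every censored man as a survivor. True survival cannot be lower than the value obtained by counting them all as dead. The overstatement is therefore at most the share censored: 8/76 = 10.5 or 11/76 = 14.5 percentage points.

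This is a ceiling. It would need every such man to die within the period analysed.

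**4. The primary rule.** Inputs from Section 6.8.3: P0 = 85%, P1 = 95%, error 5%, power 90%. The sidedness is not stated; one-sided reproduces the plan.

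- n = [(1.645 × √(0.85 × 0.15) + 1.282 × √(0.95 × 0.05)) / 0.10]² = 75.1, so 76.
- Cut-off = 76 × 0.85 + 1.645 × √(76 × 0.85 × 0.15) = 69.7, so 70.
- Exact binomial: P(X ≥ 70 | 76, 0.85) = 0.0497; power at 0.95 = 0.914.

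The design figures are correct and do not bear on the contradiction.

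**5. Illustration for pre-boost withdrawals.** Suppose two men with grade 3 toxicity in the first phase were left out and replaced. The result 70/76 (92.1%) passes. Counting them gives 70/78 (89.7%). At n = 78 and p = 0.85, the probabilities of at least 70, 71 and 72 are 0.154, 0.0855 and 0.0415, so 72 would be needed. The conclusion changes only if 70 or 71 of 76 are observed; at P1 the chance of 72 or more is 0.669.

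More generally, let w men be withdrawn and replaced, let a share q of them have grade 3–4 toxicity, and let the true toxicity-free rate in all 76 + w be 85%. The toxicity rate in the retained 76 is [0.15 × (76 + w) − q × w] / 76. The probability of declaring success is then:

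| w | q = 15% | q = 50% | q = 100% |
|---|---|---|---|
| 2 | 0.050 | 0.076 | 0.133 |
| 4 | 0.050 | 0.113 | 0.300 |

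There is no inflation if the withdrawn carry average toxicity. The values of w and q are assumptions; the protocol gives neither.

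**The case against.** The strongest reply is that the protocol already limits the loss. Section 7.5 and Appendix 2 can be read as the operative rules. Section 6.6.5 requires a final evaluation with late toxicity at premature exit under 6.5. Section 6.7.1 keeps related late serious events declarable without time limit and allows monitoring after exit. All of this stands, and it means that not every later event is lost: that would follow only if 6.5 overrode 7.5. It does not remove the contradiction, and an exit visit with serious event reporting does not replace scheduled grading or survival follow-up.

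Other readings are tempting but unsupported:

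- A reader might infer that first-phase toxicity drops out of the 70/76 count. No sentence says so. The one-session rule sits under efficacy, Section 6.8.3 does not define evaluable for toxicity (which an analysis plan may do), Section 6.6.2 grades tolerance weekly in the first phase, and the Synopsis phrase gives a sample size, not an analysis population.
- A reader might take Section 6.4 to remove everyone who misses the boost because of toxicity. Tracking and marker failures are technical, and dose-volume constraints are a planning matter. A delay could follow from toxicity, but the protocol does not say that it does. Section 7.3.1 sends some linear accelerator patients to conventional irradiation without saying that they leave the study.
- A reader might assume that a PSA rise alone triggers exit. Section 6.5 does not define progression, the Synopsis describes it as clinical or radiological for time to progression, and Section 6.7.3 treats biological progression separately.
- Nothing confines the boost-done item in Section 6.7.4 to boosted patients, so it is not shown to be uninformative.

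**Conclusion.** The contradiction between Section 6.5, Section 7.5 and Appendix 2 is established from the text and should be fixed. If 6.5 is followed, censoring depends on prognosis, overall and metastasis-free survival tend to be biased upwards, and non-serious late toxicity after progression is not graded on schedule. The size is unknown. The ceiling of 10.5 to 14.5 points on overall survival rests on an assumed 10–15% progression rate and will overstate the likely effect.

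The toxicity denominator is a weaker matter. The protocol does not show that anyone is wrongly left out of the 70/76 rule, so 70/78 is an illustration under assumption and not a demonstrated error. What remains is that Section 6.4 ends participation for some men already exposed to radiotherapy, while the primary objective covers the whole sequence. That supports continued follow-up and a supportive analysis; it does not show that the primary result would be wrong.

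**What to change.** - Reconcile Sections 6.5 and 7.5 and Appendix 2 by separating the end of protocol treatment from the end of follow-up. Progression should not end the collection of survival, metastasis and late-toxicity data at the visits already scheduled.
- Reword Section 6.4 in the same way, so that patients withdrawn before the boost continue to be followed for toxicity and survival. This concerns data collection only and leaves the clinical conditions as they are.
- Keep the 70/76 rule, and as a supportive analysis report grade 3–4 toxicity in all patients who started radiotherapy.

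The cost is a protocol amendment, a few extra attendances at visits already in the schedule, and possibly a less favourable toxicity rate in the supportive analysis.
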